#### Placebo

The placebo tablets will consist of microcrystalline cellulose, magnesium stearate (anti-caking agent) and silicon dioxide. The placebo tablets were manufactured and analysed by the Pharmia pharmaceutical company in Finland. The placebo arm will receive placebo tablets to be taken daily for the last 4 weeks of the study. The participants will not know whether they are randomised into the magnesium arm or the placebo arm. The packaging and the appearance of the placebo and magnesium tablets are identical.

### Criteria for discontinuing or modifying allocated interventions {11b}

The allocated intervention can be discontinued at any stage of the study in response to harm or the participant’s request. Possible harms are, for example, an allergy to the material of compression stockings, allergy to an ingredient of either magnesium or placebo tablets, magnesium-induced diarrhoea or inability to find suitable compression stockings. Participants can drop out of the study at any time for any reason without consequences. Any harms reported to the research assistant will be recorded. Allocated interventions cannot be modified.

### Strategies to improve adherence to interventions {11c}

Our strategy to improve adherence during the 8 weeks of follow-up is to keep in active contact with the participants via a dedicated research assistant. The participants will receive an e-mail from the research assistant including a link to the weekly questionnaire once a week during the study. In case the questionnaire is not returned, the research assistant will contact the participant by e-mail and further by phone, when necessary.

### Relevant concomitant care permitted or prohibited during the trial {11d}

The use of any magnesium products or compression stockings other than those used as the interventions of the study is prohibited during the trial. Any other medications and supplements in use will be recorded and should be continued regardless of the study.

### Provisions for post-trial care {30}

Tampere University has continuous patient indemnity insurance that covers all its medical trials. If a participant experiences any harm related to this study, the indemnity is claimed from that insurance. It covers health care treatment injuries specified in the Finnish patient injury law. The Finnish Patient Insurance Centre is responsible for handling claims.

### Outcomes {12}

#### Primary outcome

The change in the quantity of leg cramps from the 4-week follow-up period (prior to intervention) to the 4-week intervention period.

The change in the quantity of leg cramps will be assessed based on the participants’ responses to the electronic questionnaires. The quantity of cramps will be recorded using a weekly online survey during the 4 weeks before intervention and during the 4-week intervention period. The difference between the number of cramps from the 4-week period prior to the intervention to the intervention period will be calculated.

#### Secondary outcomes

The change in intensity of leg cramps from the 4-week follow-up period (prior to intervention) to the 4-week intervention period.

The possible change in the intensity of leg cramps on a visual analogue scale from 1 to 10 will be assessed based on the participants’ responses to the electronic questionnaires. The intensity of cramps will be recorded using a weekly online survey during the 4 weeks before intervention and during the 4-week intervention period. The possible change in the intensity of cramps from the 4-week period prior to the intervention to the intervention period will be assessed.
2.The change in the quantity of nocturnal awakening due to the cramps from the 4-week follow-up period (prior to intervention) to the 4-week intervention period

The change in the quantity of nocturnal awakenings due to the cramps will be assessed based on the participants’ responses to the electronic questionnaires. The participants will record this data at the end of each week and are also instructed to keep their own cramp diary. The quantity of nocturnal awakening due to the cramps will be recorded using a weekly online survey during the 4 weeks before intervention and during the 4-week intervention period. The change in the number of nocturnal awakenings due to the cramps from the 4-week period prior to the intervention to the intervention period will be calculated.

### Participant timeline {13}

### Sample size {14}

The projected number of participants is based on sample size calculations, in which a power of 80% and significance level of 0.05 will show a difference between the intervention groups in the reduction of the quantity of leg cramps when variance analysis is used in statistical testing. The calculations for the minimum sample size are based on three of Cohen’s (1988) suggested effect sizes for *f* variance analysis. When the effect size of 0.25 and a drop-out rate of 30% are used, the number of applicable participants should be a minimum of 225 persons.

### Recruitment {15}

The participants will be recruited to the study by using Google advertisements and the Finnish health library’s website article on cramps [11]. The participants will also be recruited from Finnish primary health care centres. Additional information will be sent via e-mail to those interested and providing contact information. The additional information will include information on the study (including study protocol, possible advantages and downsides, informed consent) and a link to an electronic baseline questionnaire. A consent form will be sent by post along with a request to sign and return it to the principal investigator.

## Assignment of interventions: allocation

### Sequence generation {16a}

After completing the baseline evaluation, eligible participants will be allocated to the compression stocking group, the magnesium group or the placebo group in a 1:1:1 ratio by an independent investigator using a computerised random number generator. The allocation will be stratified concerning age. To prevent selection bias, the research assistant who takes care of posting the interventions will be the only person to know each participant’s group assignment prior to treatment. The randomisation has strict limits regarding authority; no one can check the files except the principal investigator.

### Concealment mechanism {16b}

The allocation will be made by an independent investigator who provides the random sequence and group assignment to the research assistant, who will be the only person to have the information. The recruiters assessing a study subject’s eligibility based on the baseline questionnaire will not be aware of the study group to which the next participant will be assigned to, so the recruiter’s decision to enrol a participant is not influenced by any knowledge of the group. The participants are unaware of the group in which they will be allocated when they join the trial, so the decision to provide informed consent is not influenced by the knowledge of the group to which they will be allocated. During the follow-up period prior to the intervention, the intervention allocation of the study participants will be informed to the research assistant who takes care of posting the intervention.

### Implementation {16c}

Participants will be enrolled by the research assistant and research teams who will assess a study subject’s eligibility based on the baseline questionnaire. The independent investigator will generate a randomisation sequence with a computerised random number generator and the block size of 3. The randomisation sequence and group assignment are then provided to the research assistant.

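### The allocation sections contradict each other: the research assistant who enrols participants also receives the randomisation sequence, in fixed blocks of 3

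*Protocol article*

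**What the plan says.** Three neighbouring sections of the protocol article describe allocation.

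- **Implementation {16c}**, on who enrols: "Participants will be enrolled by the research assistant and research teams who will assess a study" subject's eligibility from the baseline questionnaire. The sequence comes from an independent investigator, using a "computerised random number generator and the block size of 3". Then: "The randomisation sequence and group assignment are then provided to the research assistant".
- **Concealment mechanism {16b}** agrees that the independent investigator "provides the random sequence and group assignment to the research assistant, who will be the only person to have the information". It also says that recruiters who assess eligibility "will not be aware of the study group to which the next participant will be assigned to". Its last sentence puts the disclosure of allocations to the assistant in the follow-up period before the intervention.
- **Sequence generation {16a}** sets a 1:1:1 ratio stratified by age, after the baseline evaluation. It presents the assistant's sole knowledge of assignments before treatment as the protection against selection bias, and adds that "no one can check the files except the principal investigator".

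Procedure for unblinding {17b} says that the independent investigator also knows the allocations. Who will be blinded {17a} says that the sequence stays concealed until the study ends.

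The assistant has later contact with participants too. When a weekly questionnaire is missing, "the research assistant will contact the participant by e-mail and further by phone, when necessary". Under {22}, the assistant also receives reports of harms.

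**The concern.** Concealment requires that whoever admits a participant cannot know or infer the next assignment. Here the person said to hold the assignments is also named as enrolling participants. The feature that {16a} offers as the safeguard is therefore the feature that puts it at risk.

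The opening for bias is real in this trial. Under Eligibility criteria {10}, suitability is decided from a self-completed questionnaire, and several exclusions call for judgement: suspected arterial disease, the gravity of a neuropathy, a limb whose shape or size would not suit stockings. Some of these bear directly on wearing stockings, so knowing that a stocking slot is next could affect who is accepted. Analysis cannot reliably repair selection of that kind. The stocking arm is open and all outcomes are self-reported, so sound allocation is one of the main protections left.

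A fixed block of 3 with three arms adds to the problem, because each block holds each arm exactly once and the block size is published.

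**Working it through.** The plan gives no figure for predictability, so there is none to reproduce. The check is a comparison of the sections followed by short arithmetic.

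**Step 1. The sections side by side.**

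| Question | {16a} | {16b} | {16c} |
|---|---|---|---|
| Who enrols? | not stated | recruiters, unaware of the next assignment | research assistant and research teams |
| Who gets the sequence or assignments? | assistant alone before treatment; principal investigator may check files | assistant alone | assistant |
| When? | allocation after baseline evaluation | allocations disclosed during the run-in | after the sequence is generated |

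If the assistant is one of the recruiters in {16b}, then {16b} and {16c} conflict. If not, {16c} is wrong to name the assistant as enrolling. Separately, {17b} conflicts with the statements in {16a} and {16b} that only the assistant knows.

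**Step 2. Sequence handed over before enrolment ends.** The assistant can foresee every assignment, whatever the block size.

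**Step 3. Allocations disclosed only during each participant's run-in.** Inputs: three arms, 1:1:1 ({16a}); block size 3 ({16c}). Assumptions: enrolment is rolling, and the enroller knows the age stratum, the enrolment order and all earlier assignments in the block. The chance of a correct best guess is then:

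- first place: 1/3
- second place: 1/2
- third place: 1 (certain)

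Mean = (1/3 + 1/2 + 1)/3 = 11/18 = 61.1%, against 33.3% by chance. One assignment in three is certain. A simulation of 200,000 blocks gave 61.1% and 33.3%.

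For the planned 225 participants in complete blocks, that is 225/3 = 75 certain assignments, and 225 × 11/18 = 137.5 correct guesses against 225/3 = 75 by chance.

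**Step 4. How delayed disclosure lowers this.**

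- Only the first assignment of a block known when the other two people are enrolled: (1/3 + 1/2 + 1/2)/3 = 44.4%, none certain.
- Nothing in the block yet known: 33.3%.

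So run-in disclosure gives a range from 33% to 61%, depending on the pace of enrolment. The article does not give that pace; it says only that pilot recruitment was slower than expected. Slow recruitment moves the figure towards the upper end.

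**Step 5. Larger blocks, same assumptions, block size known.**

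| Block size | Certain | Correct guesses |
|---|---|---|
| 3 | 33.3% | 61.1% |
| 6 | 20.0% | 56.1% |
| 9 | 14.3% | 53.2% |

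The figures for 6 and 9 come from the same simulation. The certain shares can be confirmed by hand as the expected closing run of a single arm: (1 + 1/5)/6 = 20.0% and (1 + 2/8 + 2/8 × 1/7)/9 = 14.3%. Larger blocks help only modestly. A mixture of undisclosed sizes was not calculated.

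**The case against.** The strongest reply is about timing. {16a} allocates after the baseline evaluation, and {16b} says that allocations reach the assistant during the run-in, hence after that participant's own eligibility decision. This stands in part: no section says that the whole list is handed over before enrolment ends. But {16b} and {16c} both say that the sequence itself goes to the assistant, and run-in disclosure still reveals past assignments to someone who goes on enrolling. Concealment would be intact if nobody were enrolled after the first disclosure, which the article does not say.

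Second, the clause on assessing eligibility in {16c} may attach to the research teams alone; {10} speaks of the researchers deciding, and {16b} treats recruiters and assistant separately. That is a fair reading, but the assistant is still named as enrolling.

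Third, a condensed article may leave the release procedure to the full protocol. That would excuse silence. Here the article states a procedure and contradicts it.

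A reader might also draw three stronger inferences, none of which the text supports:

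- **That there is no concealment at all.** The other recruiters are said to be unaware, and full foreknowledge depends on when the list is handed over.
- **That the tablet arms are wrongly described as blinded.** {8} and {17a} claim blinding only for participants in the tablet arms and for the statisticians. An assistant who knows the tablet type is a weakness, not a contradiction. Participants enter outcomes themselves, reminders follow a common weekly rule, and differential follow-up is only a possibility.
- **That the principal investigator could steer enrolment.** {16a} lets this person check the files, but no section specifically gives them an eligibility role.

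**Conclusion.** The contradiction between {16b} and {16c} is real, and it defeats the safeguard claimed in {16a} for one person, the research assistant. Its size depends on a point that the article leaves ambiguous:

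- If the sequence is handed over before enrolment ends, the assistant can foresee every assignment.
- If allocations are disclosed only during the run-in, up to one in three is certain and up to 61% can be guessed, against 33% by chance. These are upper limits under the assumptions of step 3; lagged disclosure brings them down.

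The text shows that selection is possible, not that it occurred. The point should still be corrected, because the bias could not be reliably removed afterwards and the remedy is cheap.

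**What to change.** 1. **Reconcile {16a}, {16b}, {16c} and {17b}.** State who enrols, who judges eligibility, who holds the sequence, and when each assignment is released and to whom.
2. **Separate the roles.** Give no enrolment or eligibility role to anyone who holds the sequence or past assignments. Alternatively, have the independent investigator keep the list and release each assignment only after that person's eligibility and consent are locked. The second option closes the route through the list but not inference from past assignments, so it needs step 3 as well.
3. **Change the blocks for remaining participants.** Use randomly varying sizes within age stratum, not disclosed to trial staff. This is a modest gain and does not replace step 2.
4. **Mask the tablets from the assistant, as an inexpensive addition.** Supply only the word stockings or a coded tablet kit number. The packs are already identical, so the person who chases questionnaires and receives harm reports need not know magnesium from placebo.

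The cost is a short amendment, a change of roles and a regenerated list for people still to be enrolled. No extra post is evident, since the independent investigator already exists. Enrolment began in May 2021, so the change should be prompt, and the trial report should state the procedure used before and after it.

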### Eligibility criteria {10}

Baseline information will be collected with an electronic questionnaire e-mailed to self-identified possible study subjects who have filled out an electronic contact information form. Based on the questionnaire, the researchers will decide whether the participants are suitable to participate in the study and the unsuitable individuals will be excluded at this stage. The subjects must have a functioning Internet connection and e-mail in active use to be able to participate.

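### The research assistant both enrols participants and receives the random sequence, so allocation concealment is not assured as written

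*Protocol article*

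**What the plan says.** All references are to the protocol article.

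- **Who enrols.** Implementation {16c}: "Participants will be enrolled by the research assistant and research teams". A relative clause then adds that eligibility is judged from the baseline questionnaire.
- **Who receives the sequence.** Implementation {16c}: "The randomisation sequence and group assignment are then provided to the research assistant". Concealment mechanism {16b} says the same of the independent investigator, who "provides the random sequence and group assignment to the research assistant, who will be the only person to have the information".
- **What is claimed.** Concealment mechanism {16b} says that the recruiters judging eligibility "will not be aware of the study group to which the next participant will be assigned to".
- **Timing.** Sequence generation {16a}: "After completing the baseline evaluation, eligible participants will be allocated to the compression stocking group, the magnesium group or the placebo group". Concealment mechanism {16b}: "During the follow-up period prior to the intervention, the intervention allocation of the study participants will be informed to the research assistant".
- **Discretion.** Eligibility criteria {10}: on the basis of the questionnaire, "the researchers will decide whether the participants are suitable to participate in the study".
- **Block structure.** Allocation is 1:1:1 and stratified by age ({16a}), in blocks of 3 ({16c}). The number of age strata is not given.

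**The concern.** Concealment at enrolment means that whoever accepts or refuses a volunteer cannot know which arm comes next. Here one role takes part in enrolment and also holds the information that must be hidden from those who enrol. Section {16a} presents the assistant's sole knowledge of assignments as the protection against selection bias. That protection works only if the assistant has no influence on who enters, or in what order.

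Acceptance is not purely mechanical. Several exclusion criteria call for judgement from a questionnaire, such as suspected arterial disease, the gravity of a neuropathy, or a leg shape that might not suit a stocking. The order in which self-referred volunteers are processed is a second lever.

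The stakes are highest for the stocking comparisons. That arm is unblinded and the outcomes are self-reported, so comparability at entry carries much of the weight. Imbalance introduced at enrolment cannot be fully repaired in the analysis. Moreover, the concealment statement in {16b} could not be reported as true if {16c} was followed literally.

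**Working it through.** **Step 1: set the statements side by side.**

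(a) The assistant is among those who enrol ({16c}).
(b) The assistant receives the sequence as well as the individual assignments ({16b} and {16c}).
(c) Recruiters who judge eligibility do not know the next assignment ({16b}).

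If the assistant is one of the recruiters and holds the sequence while recruitment is open, (a) and (b) contradict (c). They can be reconciled if the assistant has no part in the eligibility decision, or if nothing that reveals a future assignment reaches the assistant before that decision. The document states neither condition. It does not say that the part of the sequence covering people not yet enrolled is withheld. Nor does it say that the enrolling and posting assistants are different people; it uses the singular role throughout.

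**Step 2: what the assistant could know under each reading.** The plan gives no figure for predictability, so there is none to reproduce. Its sample size does not enter the argument; 225 serves only as the length of the simulated sequence.

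Inputs: three arms at 1:1:1 ({16a}) and a fixed block of 3 ({16c}), so each block contains each arm once.

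- *Nothing known:* chance of a correct guess = 1/3 = 33%.
- *All past assignments known, future ones not:* the chance is 1/3 for the first place in a block, 1/2 for the second and 1 for the third. The mean is (1/3 + 1/2 + 1)/3 = (11/6)/3 = 11/18 = 61%. One place in three is known with certainty; in one unstratified list that is 225/3 = 75 assignments.
- *Full sequence known:* every next arm is known.

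**Step 3: does age stratification change this?** Because the number of strata is not stated, 1, 2 and 4 were tried as an assumption, with 225 participants and 2,000 simulated trials each, and all past assignments known within the stratum.

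| Age strata (assumed) | Mean correct guesses | Next assignment certain |
|---|---|---|
| 1 | 0.610 | 0.333 |
| 2 | 0.610 | 0.330 |
| 4 | 0.607 | 0.327 |

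Stratification makes almost no difference.

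**Step 4: what the middle reading assumes.** The 61% requires that the assistant knows the block size and the stratum. It also requires enrolment staggered enough for earlier assignments in the block to have been disclosed before the next person is judged. Staggering is an assumption, made plausible by the slow recruitment reported under Pilot study. Disclosure may come at any point in the 4-week run-in. If a whole block is accepted before any of its assignments is disclosed, the guess rate for that block falls back to 33%. The 61% is therefore the upper end of this reading.

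**The case against.** The strongest counter-argument is timing. Section {16a} places allocation after the baseline evaluation, {16b} has the assistant informed during the run-in, and {16c} mentions enrolment first and says the sequence is *then* provided. Read together, these allow each person's arm to reach the assistant only after that person has been accepted. A reader might infer that the assistant holds the complete list at every eligibility decision, so that concealment fails and the next arm is always known. The document does not support that, because it never says when the list, as distinct from individual assignments, changes hands.

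The assistant's part in eligibility is also open to argument. In {16c} the clause about assessing eligibility may attach to the research teams alone, and Eligibility criteria {10} gives the decision to the researchers. The assistant's enrolment role might be purely administrative. Further safeguards stand: an independent investigator generates the sequence, the research teams are not given it, and participants consent without knowing their arm.

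These points remove the claim that concealment is shown to fail. They do not restore assurance. Both {16b} and {16c} hand over the sequence itself, {16c} names the assistant among those who enrol, and later disclosure of each person's own arm does not prevent inference about the next person from past assignments under a fixed block of 3.

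**Conclusion.** The point holds as an internal contradiction that leaves concealment unassured. It does not hold as a demonstration that concealment fails or that selection bias will occur.

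An enroller's chance of naming the next arm runs from 33% (nothing disclosed) through 61% with about one third certain (past assignments known, fixed block of 3, staggered enrolment assumed) to complete knowledge (full sequence held). The document does not settle which of these applies.

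A reader might go on to convert this into a shift of the stocking mean. That would need two inputs the document does not give: the share of places steered, and how far a person's later change in cramp count can be foreseen from a baseline questionnaire. Any such figure would only rescale assumed values, so no size of bias is claimed here. The case for acting rests on the conflict between {16b} and {16c}, the predictability of short fixed blocks, and the low cost of the remedy.

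**What to change.** 1. Let only research team members who have access neither to the sequence nor to past assignments decide eligibility and enrol. Limit the research assistant to posting interventions and contact with participants.
2. Have the independent investigator keep the sequence and release to the posting assistant one assignment per participant code, only after that participant's eligibility decision has been logged and locked.
3. Remove the hand-over of the sequence from both Concealment mechanism {16b} and Implementation {16c}; changing only one would leave the conflict in place. Then make {16a} to {16c} agree on who knows what and when. This includes {16a}, which calls the assistant the only person to know assignments yet lets the principal investigator check the files.
4. Trial status says enrolment began in May 2021. Apply the new split to the remaining participants. For those already enrolled, document who held the sequence or past assignments, from what date, and who made each eligibility decision, so that the concealment statement in the report is accurate.

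The cost is one extra message per participant and a changed division of tasks among existing staff. Sample size, interventions and outcomes are untouched. With the split in place, the fixed block of 3 gives no advantage to those deciding eligibility, provided they do not learn past assignments by another route.

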## Assignment of interventions: blinding

### Who will be blinded {17a}

The participants assigned to the two tablet groups will be blinded to the intervention. The magnesium and placebo tablets that are used in the trial will be identical in terms of packaging and appearance. The compression stocking group cannot be blinded, but the participants will not know their allotted intervention until they have received it by mail delivery. The statisticians will be blinded to the group allocation by using codes to label the three groups and will randomly assign outcome assessors to the follow-up. The allocation sequence will be concealed until the end of the study. The allocation code will be stored in a separate file.

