### Procedure for unblinding if needed {17b}

Each participant will have a personal identification code that is asked in every questionnaire of the study. The identification code acts as a link between the study material and the participants’ identifying information. The independent investigator who has done the randomisation will know the allocated intervention and can unblind it if needed in case of serious adverse effects.

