### Adverse event reporting and harms {22}

Based on the literature and previous experience, only minor adverse events are expected. Any adverse events and harms reported to the research assistant will be discussed immediately within the research group.

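### A single published block size of 3 for three arms, one of them open, makes allocation needlessly predictable to anyone who knows earlier assignments

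*Protocol article*

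**What the plan says.** All references are to the protocol article.

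- Sequence generation {16a}: allocation is "in a 1:1:1 ratio by an independent investigator using a computerised random number generator", and "The allocation will be stratified concerning age". The number of age strata is not given.
- Implementation {16c}: the sequence is produced "with a computerised random number generator and the block size of 3". No variation in size is mentioned. The same section states: "Participants will be enrolled by the research assistant and research teams". It then passes the sequence and the group assignments to the research assistant.
- Concealment mechanism {16b}: recruiters are said not to know the group of the next participant. The assistant learns the allocations during the untreated run-in.
- Who will be blinded {17a}: "The compression stocking group cannot be blinded", whereas "The participants assigned to the two tablet groups will be blinded to the intervention".
- Procedure for unblinding {17b}: the independent investigator knows each allocation and "can unblind it if needed in case of serious adverse effects".
- Adverse event reporting and harms {22}: "Any adverse events and harms reported to the research assistant will be discussed immediately within the research group".

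**The concern.** When the block size equals the number of arms, each complete block contains exactly one stocking, one magnesium and one placebo assignment. Two things follow.

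1. **Concealment.** Past assignments reveal future ones. Eligibility is judged by researchers from a questionnaire, so a recruiter who could foresee an assignment would have room to act on it. The assurance in Concealment mechanism {16b} depends on the next assignment being unpredictable.
2. **Staff blinding.** In a complete block whose stocking member is known, the other two are one magnesium and one placebo recipient. If one is unblinded, or guessed from a side effect, the other's arm follows for anyone who knows the block order.

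The block size is printed in a public article, so the pattern is open to all staff.

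**Working it through.** **Inputs.** Three arms, 1:1:1 (Sequence generation {16a}); block size 3 (Implementation {16c}); 225 participants (Sample size {14}), that is 225/3 = 75 blocks if all are complete. The protocol gives no predictability figure to reproduce; 225 serves only as the multiplier. I assume that blocks run within age strata. The protocol mentions blocks and strata separately and does not say this outright.

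**Observer who knows every earlier arm and the enrolment order.** There are 6 equally likely orders.
- Certain predictions: the third place in each block, 1/3 = 33.3%, or 75 of 225.
- Best guess: (1/3 + 1/2 + 1)/3 = 61.1% correct, against 33.3% by chance.

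**Observer who sees only stocking or tablet.**
- Stocking in place 1: the next two are certainly tablets (2 certain).
- Stocking in place 2: the third is certainly a tablet (1 certain).
- Stocking in place 3: after two tablets the third is certainly stocking (1 certain).
- Mean (2 + 1 + 1)/3 = 4/3 per block of 3, so 4/9 = 44.4%, or 100 of 225.
- The exact arm is certain only in the last case: 1/3 × 1/3 = 1/9 = 11.1%, or 25 of 225.
- Best guess of stocking versus tablet: 77.8%, against 66.7% for always guessing tablet.

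**Effect of the run-in.** The 44.4% assumes that a stocking assignment is visible at once. Simulated with visibility 4 weeks after enrolment, certainty of stocking versus tablet at enrolment is as follows (recruitment rate and number of strata are assumptions):

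| Enrolments per week | 1 stratum | 2 strata | 4 strata |
|---|---|---|---|
| 0.5 | 9.2% | 20.1% | 30.3% |
| 1 | 1.7% | 8.9% | 20.3% |
| 2 | 0.0% | 1.6% | 9.0% |
| 5 | 0.0% | 0.0% | 0.6% |

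One enrolment per week would mean 225 weeks, over 4 years, so the upper rows describe very slow recruitment.

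**Alternatives, observer knowing all past arms.**

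| Scheme | Certain | Best guess |
|---|---|---|
| Fixed 3 | 33.3% | 61.1% |
| Fixed 6 | 20.0% | 56.1% |
| Fixed 9 | 14.3% | 53.2% |
| Random 3, 6, 9 with hidden boundaries | about 4% | about 55% |

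The last row is simulated for an observer who knows the possible sizes, taken as equally likely, and updates on every past arm.

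**The case against.** The strongest reply is that hardly anyone in this trial is placed to use the pattern.

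- **Timing.** Before treatment only the research assistant is meant to know assignments, and stockings are not worn until the run-in ends. A reader might infer from the open arm that 44% of assignments are foreseeable. The documents do not support that: 44% is a ceiling, and later members of a block may already be enrolled when the stockings appear. This objection stands.
- **Access.** Stocking and sizing problems go to the assistant by e-mail or phone. Discussion of harms within the research group would reveal some participants' arms, but the article does not show other recruiters learning every stocking assignment or the enrolment order. This also stands.
- **The assistant.** This role both enrols and receives the sequence. If the whole list is handed over, every assignment is known under any block scheme, and varied blocks alone cure nothing for that person. This stands, and the fix has to cover it.
- **Outcome blinding.** A reader might infer that the magnesium–placebo tie breaks the blinding behind the primary outcome. It does not. Remote participants enter their own counts in electronic forms, and nothing in the article tells them their place in the list or who shares their block. The investigator who unblinds already knows every allocation.

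The objection does not remove the basic point. The concealment assurance should not depend on staff failing to learn past assignments, and the block size gives away more than it needs to.

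**Conclusion.** The point holds as an inexpensive improvement to concealment and staff blinding, of minor to moderate severity. For an observer with full knowledge of past arms and enrolment order, one assignment in three is certain (75 of 225) and best guessing reaches 61%. For an observer of the open arm alone, the bound is 44% for stocking versus tablet and 11% for the exact arm. With the 4-week delay the 44% drops to about 0–30%, under assumed rates of 0.5 to 5 enrolments per week and 1 to 4 age strata. The link from one unblinded tablet recipient to the other in the block is certain, but only in a complete block whose stocking member is known, and only for staff who know the block order. The arithmetic is exact; actual exposure depends on who learns past assignments, which the article settles only in part.

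**What to change.** 1. In Implementation {16c}, replace the single block size with randomly varying permuted blocks, for example 3, 6 and 9, within age strata. Only the independent investigator should know sizes and boundaries until database lock, and the article should state that sizes vary without giving them.
2. Release each assignment to the research assistant only once that participant is irrevocably enrolled, and do not hand over the whole list. Without this step, varied blocks do not help with the one role that both enrols and receives the sequence.
3. Enrolment began in May 2021, so apply both changes to the part of the list not yet issued.

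The cost is one program setting, a changed hand-over routine and a sentence or two of text. Sample size is unaffected. The downside is a possible imbalance of a few participants per stratum when enrolment stops: an unfinished block of 9 can leave two arms up to 3 apart, against 1 for a block of 3.
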